##### FC analysis

Given the functional anatomy of DMN [18, 40], five pairs of brain areas are selected as regions of interest (ROIs): IPL, mPFC, HF+, PCC, and LTC. The masks of ROIs were generated by the WFU Pick Atlas (http://fmri.wfubmc.edu/software/PickAtlas) corresponding to the anatomical regions embedded in the automated anatomical labelling (AAL). The mean time courses are extracted from each ROI by averaging the time courses over all voxels within the ROI. To better illustrate the functional organization of DMN subregions, whole-brain and ROI-wise FC will be employed. For whole-brain FC, Pearson correlation coefficients will be calculated between each ROI and the whole brain areas embedded in the AAL atlas [41]. After Fisher’s *z* transformation, an individual FC map will be used for group-wise comparison. For ROI-wise FC, Pearson correlation coefficients will be calculated between the corrected time series of the ROIs. The absolute value of the correlation coefficient (*r*) will be used as a measure to evaluate the FC between the ROIs [42–44]. Smaller value of FC indicates decreased connectivity between DMN subregions.

#### Covariates

Sociodemographic factors (age, sex, educational level, occupational attainment, employment status, marital status, and social network), physical comorbidities (as assessed by Chronic Illness Rating Scale), health behaviours (smoking and drinking, type and amount of other leisure activities, including social, physical, recreational, and intellectual activities, as assessed by Lifestyle Questionnaire [45]), and adherence to intervention (assessed based on the records of their work) will also be measured and included in the analysis.

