**Methods:**

One hundred twelve community-living Chinese aged 55 to 75 years old with SCD but without mild cognitive impairment or dementia and with prior practice of calligraphy as defined by 1 h of calligraphy per week will be recruited through elderly social centres in Hong Kong and randomized into either control or intervention group. The control group will continue with their usual practice of calligraphy, whereas the intervention group will double their practice of calligraphy. Measurement of cognitive outcomes and neuroimaging on resting-state FC will be performed at baseline and in 6 months. Repeated measures analysis of variance will be used to assess cognitive and FC changes, with time being the within-group factor, control/intervention as the between-group measure, and important covariates (age, sex, educational and occupational attainment, health, and other lifestyle factors) controlled for.

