### Sample size {14}

#### Cognitive function

The sample size (alpha 0.05, power 0.80) required to detect significant differences in global cognitive function over 6 months as assessed by ADAS-Cog between intervention and control groups is estimated using G*Power 3.1. Based on a similar RCT of 8-week calligraphy training in local older people with MCI living in care homes [26], the effect size (ES) on cognitive outcome was estimated to be 0.56. However, because the participants of this study are younger, less frail, living actively in the community, and at an earlier stage of AD, a relatively larger cognitive response (ES=0.70) is anticipated as suggested by a previous review of complex mental activity on cognition [46]. Nevertheless, because the control group will have ongoing calligraphy practice, the additional cognitive benefits arising from doubling the participation in calligraphy in the intervention group is anticipated to be lowered by a conservative estimate of 50%. Taking into consideration the effect of covariates on the cognitive outcome and an estimated drop-out rate of 20%, a total of 112 participants will be required for this study.

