#### Functional connectivity

The sample size is calculated based on a RCT of cognitive training on memory in people with MCI (*n*=72) in which individual FC maps for the hippocampal seed were generated based on correlations between the mean signal time course within each seed region and the rest of the brain [47]. Cognitive training was found to increase FC between the hippocampus and left superior frontal lobe compared to sham, and a positive correlation (*r*=0.33; *p*=0.005) between changes in hippocampal FC and changes in the memory domain was identified. Therefore, we estimate that a sample of 70 will achieve a power of 0.80 with alpha 0.05 (two-tailed). Assuming the same dropout rate, our initial calculation of 112 participants will yield enough power for the FC-cognition analysis.

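### The outcome model is to carry at least 15 covariate terms, one of them post-randomisation adherence, on about 90 completers; this costs precision unless the set explains 17% or more of six-month change, and no R² is given

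*Protocol article*

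**What the plan says.** Four places in the protocol article bear on this.

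- **Outcomes {12}, Covariates.** The list opens with "Sociodemographic factors (age, sex, educational level, occupational attainment, employment status, marital status, and social network". It goes on to a chronic illness scale, smoking, drinking, the kind and quantity of social, physical, recreational and intellectual leisure activity, and adherence. All are to be measured and used in the analysis.
- **Statistical methods {20a}.** The cognitive and FC outcomes go into a repeated measures ANOVA (time within, arm between) with covariates controlled for. The section on non-adherence and missing data {20c} repeats that adherence is a covariate.
- **Abstract, Methods.** The list is shorter: "important covariates (age, sex, educational and occupational attainment, health, and other lifestyle factors) controlled for".
- **Sample size {14}, Cognitive function.** The total of 112 is reached "Taking into consideration the effect of covariates on the cognitive outcome" and allowing for 20% dropout. No R², correlation or number of covariates is stated.

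Table 1 collects the sociodemographic, illness and lifestyle variables at both baseline and follow-up. The text does not say which visit's value enters the model.

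**The concern.** With two visits and complete data, the group-by-time test is a test of arm on six-month change. A stable background factor that predicts only the level of ADAS-Cog is already removed by taking the difference. A covariate entered with its time interaction helps only to the extent that it predicts change. Whether or not it does, it uses a degree of freedom and adds chance imbalance between the arms. With 15 or more such terms and about 45 completers per arm, that price is not negligible, and the article gives no reason why marital or employment status, for example, should predict change.

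Adherence raises a separate difficulty. It is measured after randomisation and, if entered as time practised, follows the arm by design, because one arm is asked to practise twice as long. At stake is the precision of the ADAS-Cog and FC comparisons and, through adherence, what the arm effect means.

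**Working it through.** **Inputs.** From Sample size {14}: "The sample size (alpha 0.05, power 0.80) required to detect significant differences in global cognitive function over 6 months"; "a relatively larger cognitive response (ES=0.70) is anticipated"; this benefit is then "anticipated to be lowered by a conservative estimate of 50" per cent, so d = 0.70 × 0.5 = 0.35; 112 randomised with 20% dropout leaves 112 × 0.8 = 89.6, about 90 completers. Allocation is 1:1. Sidedness is not stated for the cognitive calculation. Two-sided is assumed, as in the FC calculation.

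**The plan's own figure.** A two-sample t test at d = 0.35 needs 260 completers, and 260/0.8 = 325 randomised; one-sided it is 204, and 204/0.8 = 255. Neither is 112. A within-between interaction run with f = 0.35/2 = 0.175 and an assumed correlation of 0.3 between visits gives 92 completers, and 92/0.8 = 115. That is near 112, but the correlation is not in the document. The 112 therefore cannot be reproduced from the stated inputs, and the part played by covariates cannot be recovered.

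**Counting terms.** 7 sociodemographic + 1 comorbidity + 2 (smoking, drinking) + 4 leisure domains = 14; with adherence, 15. This is one term each. Multi-level factors, or separate terms for kind and quantity of leisure, would raise it. Counts of 20 and 25 are shown as assumptions.

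**Variance of the arm effect.** For p covariates unrelated to arm and n completers, the expected multiplier relative to no covariates is (1 − R²) × (n − 3)/(n − 3 − p). With n = 90 this is (1 − R²) × 87/(87 − p). Break-even is R² = p/87, where R² is the share of six-month change explained. Power is from the noncentral t with 88 − p degrees of freedom, taking d = 0.35 in SD units of change.

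| Terms p | 87/(87 − p) | Break-even R² | Power, R² = 0 | Power, R² = 0.10 | Power, R² = 0.30 |
|---|---|---|---|---|---|
| 0 | 1.00 | – | 0.375 | – | – |
| 15 | 87/72 = 1.21 | 17% | 0.32 | 0.35 | 0.43 |
| 20 | 87/67 = 1.30 | 23% | 0.30 | 0.33 | 0.40 |
| 25 | 87/62 = 1.40 | 29% | 0.28 | 0.31 | 0.38 |

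Simulation (5,000 trials per cell) agrees: at R² = 0, power is 0.32 for 15 terms and 0.29 for 25. Most of the loss is chance imbalance. The critical t moves only from 1.987 to 1.993 (15 terms) or 1.998 (25 terms).

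**Adherence.** The multiplier above treats every term as unrelated to arm, so it understates the cost of adherence if that tracks arm. For assumed correlations with arm of 0.5, 0.7 and 0.9, the inflation 1/(1 − r²) is 1.3, 2.0 and 5.3. With adherence as the only covariate, power at d = 0.35 is then 0.30, 0.22 and 0.11. If adherence is entered as a percentage of each person's target, the correlation could be small.

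**The case against.** The strongest reply is that the sign is unknown. No R² is given, and above 17% to 29% of change explained the covariates add power: at R² = 0.30 all three counts do slightly better than no adjustment. That stands. A reader might infer that the covariates are more likely to cost power than to add it. The document does not support that, although a net loss is plausible for a test on change.

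A reader might also infer that the sample size counts the covariates as a help, for instance that they must explain some 66% of variance to bring 325 down to 112. The wording gives no direction. The opposite reading also fits: the interaction run with an assumed correlation of 0.5 needs 68 completers, and a penalty for 20 uninformative terms gives 68 × 1.30 = 88, or 88/0.8 = 110 randomised. Only non-disclosure can be criticised.

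Third, the final list and its coding may be settled in an analysis plan that is not shown, and the Abstract's list has about six items, for which the multiplier is only 87/81 = 1.07. This limits the upper counts, which are assumptions. It does not remove the point, because the Covariates section states its own full list and sends all of it to the analysis, and the Abstract's list differs from it.

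Fourth, adjustment for baseline variables leaves the arm effect unbiased under randomisation, and 63 to 73 residual degrees of freedom remain. That is right, and instability of the estimates is not shown. The defence does not extend to adherence or to follow-up values.

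**Conclusion.** The point holds as a cheap improvement. The article's stated rule puts at least 14 background covariates plus post-randomisation adherence into outcome models with about 90 completers. At 15 terms the arm-effect variance is multiplied by about 1.21, so the set must explain at least 17% of six-month change to pay for itself. The figures for 20 and 25 terms depend on coding the document does not give. With no explained variance, the loss at the planned effect is about 6 points of power at 15 terms and 9 at 25, on a two-sample change test whose power is already only 0.375.

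This rests on four assumptions: two-sided testing, d in SD units of change, one term per item for the count of 15, and covariates entered with their time interactions. If they enter only the between-subject part, they neither cost nor help the group-by-time test. It is not shown that the covariates reduce power on balance, nor that the 112 relied on them as a gain.

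**What to change.** - In Covariates and in Statistical methods {20a}, limit the main outcome models to a short prespecified list of baseline covariates, for example age, sex and education.
- State that only baseline (T0) values are used, and leave adherence and follow-up (T1) values out of the main model. Amend the sentence on adherence in {20c} to match.
- Put the remaining baseline variables in one labelled sensitivity model.
- Align the list in the Abstract.
- In Sample size {14}, state the assumed covariate R² or remove the reference to covariates.

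The cost is wording only. The downside is small: chance imbalance on a minor covariate is then handled in the sensitivity model and not in the main one.

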### Participant timeline {13}

The study flowchart is illustrated in Fig. 1.

**Fig. 1 Fig1:**
[figure not shown]
Study flowchart

### Sample size {14}

#### Cognitive function

The sample size (alpha 0.05, power 0.80) required to detect significant differences in global cognitive function over 6 months as assessed by ADAS-Cog between intervention and control groups is estimated using G*Power 3.1. Based on a similar RCT of 8-week calligraphy training in local older people with MCI living in care homes [26], the effect size (ES) on cognitive outcome was estimated to be 0.56. However, because the participants of this study are younger, less frail, living actively in the community, and at an earlier stage of AD, a relatively larger cognitive response (ES=0.70) is anticipated as suggested by a previous review of complex mental activity on cognition [46]. Nevertheless, because the control group will have ongoing calligraphy practice, the additional cognitive benefits arising from doubling the participation in calligraphy in the intervention group is anticipated to be lowered by a conservative estimate of 50%. Taking into consideration the effect of covariates on the cognitive outcome and an estimated drop-out rate of 20%, a total of 112 participants will be required for this study.

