## Statistical methods

### Statistical methods for primary and secondary outcomes {20a}

Statistical analysis will be performed using IBM SPSS Statistics for Windows. Independent *t* test (for continuous variables) and chi-square test (for categorical variables) will be used to compare socio-demographics, clinical characteristics, lifestyle activities, cognitive functions, and resting-state FCs at baseline between the control and intervention groups for exploratory analyses. Repeated measures analysis of variance will be used to evaluate the cognitive and FC changes, with time being the within-group factor, control/intervention as the between-group measure, and covariates being controlled for. Association between cognitive parameters and FCs will be computed with correlational analyses. Intention-to-treat analysis and Bonferroni correction will be adopted.

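### The total of 112 participants does not follow from the printed sample-size inputs unless an unstated covariate or pre-post correlation of just over 0.8 is assumed

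*Protocol article*

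**What the plan says.** The calculation is in the protocol article, Sample size {14}, under Cognitive function. Its target is set out as "The sample size (alpha 0.05, power 0.80) required to detect significant differences in global cognitive function over 6 months as assessed by ADAS-Cog". From a calligraphy trial in care-home residents with MCI, "the effect size (ES) on cognitive outcome was estimated to be 0.56". For the present younger, community-living population "a relatively larger cognitive response (ES=0.70) is anticipated". Because the control arm also practises calligraphy, the added benefit "is anticipated to be lowered by a conservative estimate of 50" per cent. The section then says that the effect of covariates was considered, allows for drop-out and gives the result: "an estimated drop-out rate of 20%, a total of 112 participants will be required for this study".

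The halved value, 0.35, is not printed but follows directly. The section names G*Power 3.1. It does not give the test family, the effect metric, the sidedness or any correlation or R-squared. The only sidedness in the article belongs to the functional connectivity calculation: "a sample of 70 will achieve a power of 0.80 with alpha 0.05 (two-tailed"). Trial design {8} fixes 1:1 allocation. Statistical methods {20a} plans a repeated measures analysis of variance with time, group and covariates.

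**The concern.** The section prints an effect, a reduction, alpha, power, drop-out and a total, so the total can be checked. It is about one third of what the printed effect requires in a plain two-group comparison (112 against 325). The only thing linking inputs to result is a reference to covariates with no number attached, and that number has to be large.

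ADAS-Cog is the primary cognitive outcome, and 0.80 is the power claimed for it. If the correlation is lower than the total needs, the trial has less chance of detecting its own target effect than the article says. A non-significant result would then say less about an effect of 0.35 than a reader relying on the stated power would think.

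**Working it through.** **Inputs from the article.** Effect 0.70 × 0.5 = 0.35. Alpha 0.05, power 0.80. Drop-out 20%. Allocation 1:1. Total 112, so completers = 112 × 0.8 = 89.6, about 90, or 45 per arm.

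**Assumptions needed to proceed.** The effect size is a standardised mean difference d, and the test is two-sided, as in the article's other calculation. The correlations used below are illustrative; the article gives none.

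**Step 1: trying to reproduce 112.** Exact two-sample t test (noncentral t, noncentrality d × √(n/2) with n per arm), randomised = completers / 0.8:

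| Effect d | Completers, two-sided | Randomised, two-sided | Randomised, one-sided |
|---|---|---|---|
| 0.35 | 260 | 325 | 255 |
| 0.56 | 104 | 130 | 103 |
| 0.60 | 90 | 113 | 90 |
| 0.70 | 68 | 85 | 65 |

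None of the article's effect sizes gives 112. The value 0.60 comes within one participant but appears nowhere in the text.

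Two other G*Power routes were tried.
- ANCOVA with f = 0.35 needs 67 completers (84 randomised). For two groups, f = 0.35 is the same as d = 0.70.
- The within-between interaction module with f = 0.175 and an assumed correlation of 0.3 needs 92 completers (115 randomised). That comes close, but it enters d/2 as the interaction effect. A difference of 0.35 present only at follow-up corresponds to f = d/4 = 0.0875, which needs 260 completers at a correlation of 0.5.

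**Step 2: power at 0.35 with the stated size, no covariate gain.** Noncentrality = 0.35 × √(45/2) = 0.35 × 4.743 = 1.660 on 88 degrees of freedom. Two-sided power = 0.375, about 0.38. With no drop-out at all (56 per arm) it is 0.45. One-sided at 45 per arm it is 0.50.

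**Step 3: the correlation that makes 112 work.** With 45 per arm, the effect detectable at 0.80 power, two-sided, is d = 0.597. To bring 0.35 up to that level the residual variance must shrink to (0.35 / 0.597)² = 0.344 of the original.
- Baseline or covariate adjustment, variance factor 1 − r²: r² = 1 − 0.344 = 0.656, so r is about 0.81.
- Group-by-time (change) contrast, variance factor 2(1 − ρ): 1 − ρ = 0.172, so ρ is about 0.83.
- If the test were one-sided, the adjusted analysis would need r of about 0.75.

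**Step 4: power at 0.35 under assumed correlations** (45 per arm, two-sided):

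| Assumed correlation | Baseline-adjusted, d/√(1 − r²) | Group-by-time, d/√(2(1 − ρ)) |
|---|---|---|
| 0.5 | 0.47 | 0.38 |
| 0.7 | 0.63 | 0.56 |
| 0.8 | 0.78 | 0.74 |

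At ρ = 0.3 the group-by-time test gives 0.28. The result depends strongly on the quantity that is not stated.

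**The case against.** The strongest reply is that the article does not claim an unadjusted comparison. It says covariates were considered, and the planned analysis adjusts for them. With r of about 0.81 or more, 112 does reach 0.80, and at r = 0.8 the shortfall is trivial (0.78). A reader might infer that the trial simply lacks 0.80 power at 0.35. The documents do not support that, because they leave the deciding correlation open. This part of the objection stands.

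The article also condenses a fuller protocol, so the test family and correlation may be recorded there. Their absence alone would not be a finding. What remains is that the printed total does not follow from the printed inputs, with only an unquantified phrase between them.

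The effect metric is open too, but reading it as f does not help: f = 0.35 gives 84 randomised, not 112.

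Three further inferences are tempting and go beyond the text.
- **That the halving was skipped.** The un-halved 0.70 needs about 85 randomised, so it does not reproduce 112 either. That 112 suits an effect of about 0.60 says what the size can detect, not how it was derived.
- **That alpha should be split across two primary outcomes.** The article says "Intention-to-treat analysis and Bonferroni correction will be adopted" but defines no family, so a particular split would be guesswork.
- **That half of 0.56 is the real target.** The article moves to 0.70 before reducing it.

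**Conclusion.** The point holds in conditional form. The total of 112 does not follow from an effect of 0.35, alpha 0.05, power 0.80 and 20% drop-out. Those inputs alone call for 325 randomised, and 45 completers per arm give power of about 0.38. The claimed 0.80 needs covariates to explain about 65% of the variance in follow-up ADAS-Cog, or a pre-post correlation of about 0.83 in the group-by-time test. Neither is stated.

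This rests on reading the effect size as a standardised mean difference and the test as two-sided. A one-sided test lowers the required correlation to about 0.75 in the adjusted analysis but does not remove the need for it. The actual power cannot be given as a single figure or a firm range until the correlation is supplied; the values at 0.5, 0.7 and 0.8 are illustrations.

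**What to change.** Restate the Cognitive function part of Sample size {14}:
- Name the effect metric, the sidedness, the G*Power test and the assumed correlation or R-squared, with its source.
- Under that assumption, give the power at 0.35 with about 90 completers, or the effect detectable at 0.80 power. Without covariate gain the detectable effect is about d = 0.60.
- If the assumed correlation is below about 0.81 (about 0.83 if the test is the group-by-time contrast), replace the 0.80 power statement with the lower figure.

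The Trial status section reports that recruitment ended on 31 December 2021, so this corrects the stated power and does not ask for a larger trial. It needs no extra participants and no change to allocation, outcomes or analysis. The cost is a stated power that may be less favourable.

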#### Functional connectivity

The sample size is calculated based on a RCT of cognitive training on memory in people with MCI (*n*=72) in which individual FC maps for the hippocampal seed were generated based on correlations between the mean signal time course within each seed region and the rest of the brain [47]. Cognitive training was found to increase FC between the hippocampus and left superior frontal lobe compared to sham, and a positive correlation (*r*=0.33; *p*=0.005) between changes in hippocampal FC and changes in the memory domain was identified. Therefore, we estimate that a sample of 70 will achieve a power of 0.80 with alpha 0.05 (two-tailed). Assuming the same dropout rate, our initial calculation of 112 participants will yield enough power for the FC-cognition analysis.

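### The power stated for the FC-cognition correlation is for one test at alpha 0.05, but the plan describes several such correlations under a Bonferroni correction whose family is not stated

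*Protocol article*

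**What the plan says.** The functional connectivity part of the sample size section takes its effect from an earlier trial of cognitive training in people with mild cognitive impairment, where "a positive correlation (*r*=0.33; *p*=0.005) between changes in hippocampal FC and changes in the memory domain was identified". From this it derives its requirement: "Therefore, we estimate that a sample of 70 will achieve a power of 0.80 with alpha 0.05 (two-tailed"). It then closes: "Assuming the same dropout rate, our initial calculation of 112 participants will yield enough power for the FC-cognition analysis". The dropout rate and total come from the cognitive part of the same section: "an estimated drop-out rate of 20%, a total of 112 participants will be required for this study".

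The section on statistical methods for primary and secondary outcomes describes the analysis in the plural: "Association between cognitive parameters and FCs will be computed with correlational analyses". The next sentence reads: "Intention-to-treat analysis and Bonferroni correction will be adopted". It does not say which tests the correction covers or how many there are.

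The FC analysis section defines the connectivity measures on several regions: "five pairs of brain areas are selected as regions of interest (ROIs): IPL, mPFC, HF+, PCC, and LTC". ROI-wise FC is one value for each pair of ROIs, and ROI-to-whole-brain maps come on top. The outcome sections list nine cognitive measures: ADAS-Cog as primary, and eight secondary (HK-MoCA, MIC, digit span forward and backward, trail making A and B, 10-minute delayed recall, verbal fluency). No section singles out one ROI pair, or one FC-cognition correlation, as the one to be tested.

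**The concern.** The sample size section states power at an uncorrected 0.05, while the analysis section announces a correction that lowers the threshold for each test. Both statements can hold only if the correlations fall outside the Bonferroni family, or if that family is small enough for the surplus of 112 over the single-test requirement to absorb the correction. The article says neither, and its lists of regions and cognitive scores point to more than a handful of tests.

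The correlation between cognitive and FC changes is the third stated objective and carries the mechanistic argument of the trial. If the analysis is run as a corrected family, a null result would be read against a stated power of at least 0.80 when the true figure could be well below that. An unstated family also leaves the divisor open to choice after the results are known.

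**Working it through.** **Inputs.** From the functional connectivity sample size section: r = 0.33, two-sided alpha 0.05, power 0.80, n = 70. From the cognitive sample size section: N = 112 and 20% dropout, so 112 × 0.8 = 89.6, that is 89 to 90 completers. From the FC analysis section: five regions. From the outcome sections: nine cognitive scores. The number of tests k in the Bonferroni family is not given and is an assumption throughout.

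**The plan's own figure.** With the Fisher z approximation, n = ((z(1−α/2) + z(power)) / atanh(r))² + 3.

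- atanh(0.33) = 0.3428
- n = ((1.960 + 0.842) / 0.3428)² + 3 = 69.8, rounded up to 70
- enrolled at 20% dropout: 70 / 0.8 = 87.5, rounded up to 88, which is below 112

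The stated 70 reproduces (power at n = 70 is 0.801). An exact bivariate-normal calculation gives 69, so the method makes no practical difference. For one correlation, the adequacy statement is correct with room to spare.

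**Possible family sizes.** Five regions with the two sides merged give 5 × 4 / 2 = 10 links. If left and right are kept apart, ten ROIs give 10 × 9 / 2 = 45. ADAS-Cog alone against these is 10 or 45 tests; nine scores against 10 links is 9 × 10 = 90. The whole-brain maps would add more.

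**Power under Bonferroni.** Use α = 0.05/k and power = Φ(atanh(r) × √(n − 3) − z(1−α/2)). For n = 90, 0.3428 × √87 = 3.198. Examples:

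- k = 1: Φ(3.198 − 1.960) = 0.89
- k = 2: Φ(3.198 − 2.241) = 0.83
- k = 3: Φ(3.198 − 2.394) = 0.79
- k = 10: Φ(3.198 − 2.807) = 0.65

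| Tests in family (k) | Alpha per test | Power, 89 to 90 completers | Completers for 0.80 | Enrolled at 20% dropout |
|---|---|---|---|---|
| 1 | 0.05 | 0.89 | 70 | 88 |
| 2 | 0.025 | 0.83 | 84 | 105 |
| 3 | 0.0167 | 0.78–0.79 | 93 | 117 |
| 4 | 0.0125 | 0.75–0.76 | 98 | 123 |
| 5 | 0.01 | 0.73 | 103 | 129 |
| 10 | 0.005 | about 0.65 | 117 | 147 |
| 45 | 0.0011 | about 0.47 | 147 | 184 |
| 90 | 0.00056 | 0.39–0.40 | 160 | 200 |

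These are powers for any one correlation whose true value is 0.33.

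**Sensitivity to dropout.** If all 112 completed, power would stay at 0.80 up to eight tests and be 0.79 at nine and 0.78 at ten. The limit of two tests therefore depends on the plan's own 20% dropout.

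**The case against.** The strongest objection is that the family is not the plan's statement. The Bonferroni sentence names no tests. It could refer to comparisons within the repeated measures model, to the outcomes, to the ROI pairs, to the correlations, or to some of these. The article is condensed, and an analysis plan that is not at hand may define the family. This stands: 10, 45 and 90 are readings of the ROI and outcome lists. It does not remove the point, because the article itself makes a positive claim of adequate power and adopts a correction without limiting its scope, and it does not reconcile them.

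It is also fair to say that the shortfall at three tests is small: 1 to 2 points of power, and 117 enrolled against 112. At that count the claim is only marginally missed.

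Three stronger readings are tempting, and the documents do not support them.

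- A reader might infer that the imaging objective becomes nearly impossible to detect. The powers of 0.40 to 0.65 concern the FC-cognition correlation and mean underpowered, no more. For the group effect on FC, which is the primary neuroimaging outcome, the article gives neither an expected effect nor a power claim to measure against.
- A reader might infer that power for ADAS-Cog falls too. The article names one primary outcome in the cognitive domain and one in neuroimaging, but does not say that they share one alpha.
- A reader might infer that the plan needs a single composite of all ROI pairs with a fixed test sequence and false-discovery-rate control. That is a design preference. It could dilute a regional effect, and the article's background expects early change in the posterior part of the network.

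**Conclusion.** The point holds as a mismatch between planning alpha and analysis alpha. The single-test calculation is correct. Under the plan's r = 0.33 and 20% dropout, the claim that 112 is enough survives a Bonferroni family of two, is marginal at three and clearly fails at larger counts. Even ADAS-Cog alone against the ten merged-region links would have power of about 0.65. The conclusion assumes that Bonferroni covers the FC-cognition correlations and that the family holds at least three of them. The article states neither, but nothing in it says otherwise and its lists of measures make both the natural reading. The matter should be settled before analysis. It is no fault in the arithmetic and no reason to doubt the rest of the sample size section.

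**What to change.** Do one of the following in the sample size and statistical methods sections, before the FC-cognition results are seen.

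1. Name one confirmatory FC-cognition correlation (one FC measure with one cognitive score), tested at the two-sided 0.05 used in the sample size section, where power is 0.89. If two are wanted, test each at 0.025, where power is 0.83. Label all other FC-cognition correlations exploratory.
2. Or state which tests form the Bonferroni family and how many there are, and restate the FC-cognition power at the resulting alpha in place of the present adequacy statement.

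The trial status section reports that recruitment ended on 31 December 2021, so the remedy is text rather than more participants. The cost of the first option is that correlations for individual ROI pairs become exploratory. The cost of the second is a less favourable power statement.
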